### Power calculation

The sample size was settled to permit a logistic regression analysis for the dichotomous primary outcome measure “remission of PTSD after two year” being regressed on three predictors: 1) duration of treatment, 2) severity of traumatic experiences, and 3) neglect. We determined the sample size by application of the rule of having ten events per variable, which is a conservative rule [39]. We expect that that the percentage of remitted patients will be in the range of 25%–75%, implying 40 observations per predictor. Studying three predictors, the rule implies a minimal sample size of 120. A further assumption of a drop-out rate of 20%, made us aim at 150 participants at baseline.

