### Data analysis

Characteristics of the study sample will be described, using frequencies of participants and non-participants after two-year follow-up. Possible (selective) differences between the completers and non-completers will be tested using chi-square test for categorical variables and t-test for continuous variables. The course of trauma-related and personality disorders will be determined by comparing the two-year follow-up outcome with the baseline diagnostic status on four variables. For the categorical variables, i.e. presence of PTSD diagnosis (yes/no) and presence of a personality disorder (yes/no), we use chi-square statistics. For the continuous variables, i.e. severity score on the CAPS for PTSD (range 0–144) and total number of criteria met for personality disorders et cetera, we use analysis of variance. We will use a Bonferroni correction for multiple testing.

The aim of the current study is to validate the model of Draijer as a prognostic model. For an extensive description of this model and the validation of the model as a diagnostic instrument, we refer to [23]. In short, two severity indexes will be constructed, one for traumatization and one for neglect, to test relationship between the severity of chronic childhood trauma and neglect, and the severity of respectively trauma-related disorders and personality disorders. We test the possibility of relating the diagnostic square to changeability of psychopathology within a period of 2 year, by using a changeability score, based on the sum of the two severity indexes at baseline (range 0–10), as a predictor in a regression analysis on the raw difference scores (i.e. CAPS-score at follow-up minus CAPS-score at baseline). In addition, the changeability score can be replaced by separate scores on severity of traumatization and severity of neglect, so we can compare the regression coefficients and test if both axis of the square are equally related to the observed change after 2 years.

Secondly, to find determinants (predictors) of the two-year course, we will use logistic regression analysis for dichotomous primary outcome measures, as descripted in the power calculation. Again, we will use a Bonferroni correction for multiple testing. The amount of predictors we will test, will be based on literature and the distribution of our data.

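### Both planned Bonferroni corrections are valid, but Holm's step-down version controls the same familywise error, never rejects less, and gains power when several effects are real

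*Protocol article*

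**What the plan says.** The Data analysis section names the multiplicity method twice.

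- For the course of the disorders, the plan is "comparing the two-year follow-up outcome with the baseline diagnostic status on four variables". Two of these are categorical and are tested by chi-square. The continuous ones are the CAPS severity score and the "total number of criteria met for personality disorders et cetera, we use analysis of variance". Then: "We will use a Bonferroni correction for multiple testing".
- For the determinants of course, logistic regression is planned for dichotomous primary outcomes, followed by: "Again, we will use a Bonferroni correction for multiple testing".

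The article gives no significance level and does not say whether the correction is single-step or step-down. Neither family is closed. The course list announces four variables but trails off in an et cetera, and for the regressions "The amount of predictors we will test, will be based on literature and the distribution of our data".

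The Power calculation section works with three predictors: "Studying three predictors, the rule implies a minimal sample size of 120".

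**The concern.** Without a qualifier, a Bonferroni correction ordinarily means comparing every p-value in a family of m tests with α/m. Holm's procedure uses α/m only for the smallest p-value, then α/(m−1) for the next, and so on until the first non-rejection. It needs no further assumption about how the tests are correlated. Any hypothesis that Bonferroni rejects, Holm rejects too.

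This matters because the cohort is closed at 150 baseline patients, so extra recruitment cannot restore lost power. Holm helps most when several effects in a family are real. The end of the Background section states that expectation for the predictors: trauma and neglect severity, and the amount and type of treatment, are all expected to predict the course. These correspond to the three predictors used for sizing.

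**Working it through.** **1. The plan's own figures.** The Power calculation section states: "We determined the sample size by application of the rule of having ten events per variable, which is a conservative rule". It expects that "the percentage of remitted patients will be in the range of 25%–75%, implying 40 observations per predictor".

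- Observations per predictor: 10 / 0.25 = 40.
- Three predictors: 3 × 40 = 120.
- With 20% drop-out: 120 / (1 − 0.20) = 150.

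Both stated figures reproduce. Neither uses a significance level, so the choice of correction cannot change them.

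**2. Validity of what is planned.** With m independent true nulls each tested at 0.05/m, the familywise error is 1 − (1 − 0.05/m)^m. This gives 0.0492 for m = 3 and 0.0491 for m = 4. Bonferroni does its job.

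**3. Ordered thresholds** (5% familywise level assumed).

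| Family | Bonferroni, every p-value | Holm, smallest to largest p-value |
|---|---|---|
| m = 3 (predictors in the sizing) | 0.0167 | 0.0167, 0.025, 0.05 |
| m = 4 (course variables announced) | 0.0125 | 0.0125, 0.0167, 0.025, 0.05 |

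The first threshold is the same under both methods. A gain can arise only after one hypothesis has been rejected.

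**4. Power under Bonferroni.** The article gives no effect size. I assume an expected z of 2.8 for each real effect, which means about 80% power at an unadjusted two-sided 5% level: Φ(2.8 − 1.96) = 0.80. A correlation of 0.25 at N = 120 gives the same value: 0.25 × √118 / √(1 − 0.0625) = 2.80. This serves only as a yardstick. It is not derived for a multivariable logistic coefficient or for a change from baseline.

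- m = 3: critical z = 2.394, power = Φ(2.8 − 2.394) = 0.658.
- m = 4: critical z = 2.498, power = Φ(2.8 − 2.498) = 0.619.

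**5. Power under Holm**, by simulation (400,000 sets of z-statistics per scenario, correlation between tests 0 to 0.3).

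| m | Real effects | Bonferroni, per real effect | Holm, per real effect | All real effects found, Bonferroni | All real effects found, Holm |
|---|---|---|---|---|---|
| 3 | 3 | 66% | 74–75% | 29–36% | 49–55% |
| 3 | 2 | 66% | 69–70% | 43–48% | 51–54% |
| 3 | 1 | 66% | 66% | 66% | 66% |
| 4 | 4 | 62% | 72–73% | 15–24% | 38–47% |
| 4 | 3 | 62% | 67–68% | 24–32% | 36–43% |
| 4 | 2 | 62% | 64% | 38–43% | 43–47% |
| 4 | 1 | 62% | 62% | 62% | 62% |

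At a correlation of 0.5, Holm's per-test power with all effects real is slightly lower: 73% (m = 3) and 71% (m = 4).

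Three further results hold in every scenario:

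- The chance of finding at least one real effect is the same under both methods to within 0.2 percentage points.
- Familywise error under Holm stays below 5%. With exactly one true null it is 3.1–3.7%, against 1.2–1.7% under Bonferroni.
- Bonferroni never rejected a hypothesis that Holm did not.

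**The case against.** The strongest reply is that nothing here is wrong. Bonferroni is valid and familiar, it contradicts nothing in the article, and no stated figure rests on it. That stands: this is a point about efficiency. A reader might infer from it that the plan's error control is faulty or that the study is too small. The documents support neither inference on this ground, since the familywise error is held and the sizing uses no α.

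Four limits also stand.

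- **The single-step reading is inferred.** It is the usual meaning, but the article states neither it nor a significance level. The values 0.0125 and 0.0167 follow from an assumed 5%.
- **The families are open.** Three predictors is the sizing model, not a declared test family, and the course list is not closed. Holm needs a fixed family as much as Bonferroni does, so changing the method alone does not cure this.
- **The gain is conditional.** A reader might take Holm to give more power whatever the truth, but with a single real effect it gives essentially none. The Background expects several real effects among the predictors. It does not predict change on all four course variables: it describes these disorders as mostly chronic, and the Discussion does not expect uniformly favourable courses. The four-out-of-four row is therefore an upper case, not the plan's own scenario.
- **The change is not entirely free.** Bonferroni has simple matching simultaneous confidence intervals and Holm does not. This has some weight in a study that will interpret regression coefficients.

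One part does not stand: that the choice can be left alone because an article leaves details to an analysis plan. The article names the method, twice. If a step-down version was meant, the same edit makes that clear.

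**Conclusion.** The point holds as a cheap improvement, not as an error. Holm matches Bonferroni's familywise control under any dependence and can only add rejections.

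The case is firmest for the predictor regressions, where the plan itself expects several real effects. If all three are real, per-test power rises by about 8–9 points; if two are real, by 3–4 points. For the course comparisons the gain runs from zero to about 11 points, depending on how many of the four variables truly change.

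These sizes rest on a 5% familywise level, an expected z of 2.8 per real effect, correlations between tests of 0 to 0.3, and families of three and four. The ordering of the two methods rests on none of these assumptions.

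**What to change.** In both sentences of the Data analysis section, replace the Bonferroni correction with a *Holm (step-down Bonferroni) correction*, and state the familywise significance level. Apply it within each family once its members have been listed, before outcome data are examined: close the list of course variables, and name the predictors and dichotomous outcomes to be tested. Report Holm-adjusted p-values, with confidence intervals labelled as unadjusted.

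The cost is a few words for the method and a short list for the families. No patients, visits or measurements are added. Matching simultaneous intervals become less simple, and an unadjusted interval may exclude the null where Holm does not reject, so the report should say that the adjusted p-value decides.

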## Discussion

As with most follow-up (longitudinal) studies, the biggest challenge of this study is to reach all patients who participated in the baseline study [23]. Response rates in follow-up studies vary from 58% to 94% [2, 3, 14, 15, 22]. While the treatment of (complex) trauma-related disorders and personality disorders tend to take a long time, chances of patients still having therapy within GGZ Friesland are rather high. This makes it easier to contact patients and lowers the risk of expired telephone numbers and old addresses. However, while at baseline assessment was part of daily clinical routine for patients referred to trauma-related disorders program, the follow-up assessment is not embedded in any particular treatment program. This could lower the response rates. We expect non-response due to patients who are not able to participate (due to i.e. emigration, physical illness or death by suicide), patients who are not willing to participate (due to i.e. lack of time or motivation) and patients which cannot be reached (due to i.e. changed telephone numbers, changed addresses). To minimalize non-response during the study period, we keep in close touch with the treatment departments and treating clinicians. Furthermore, patients get well informed, we create a pleasant atmosphere during assessment and we concern (and anticipate on) the patients’ needs, as far as possible. All risks considered, we expect a non-response rate of 20%, leaving an N of 120. This N provides enough statistical power to answer the research questions.

Using the same psychologists to conduct the assessments at baseline and follow-up has both advantages and disadvantages. Psychologists must be well trained and have clinical expertise to obtain the clinical interviews in a reliable way. Psychologists meeting those criteria are scarce. The inter-rated agreement intervals were high at baseline (.90 to.95). Using other psychologist at follow-up can lower the inter-rated agreement. On the other hand, using the same psychologist can result in a bias towards a favourable course. However, we do not expect solitary favourable courses in our hypothesis. To minimalize any form of bias, psychologists are not allowed to look-up (individual) outcome at baseline, before they conduct follow-up assessment. Furthermore, we provide personal supervision by a senior clinical psychologist and encourage to reason the scoring of clinical interviews to enhance objectivity.

We overcome limitations of previous studies, as discussed above, by using structured clinical interviews as well as symptom questionnaires, carefully registering onset and type of trauma (at baseline and follow-up) and collecting several data, which potentially act as predictors of course of disorders and symptoms. Furthermore, to keep track of factors that may affect symptom change, we enumerate use of medication, received therapy (in- and outside GGZ Friesland) and traumatic experiences in the two-year period after baseline assessment. Also, we keep track of developments, like changes in offered therapies in the specialized treatment programs (of trauma-related and personality disorders) at GGZ Friesland. However, we cannot overcome some limitations, inherent in this type of research, like the use of retrospective data. Also, in addition to the clinical interviews, we use some self-report questionnaires.

An important strength of this study is that it is unique in the elaborate way in which traumatization and (personality) pathology are investigated [23]. This study will provide insight in the relation between symptoms of trauma-related disorders and personality disorders and how they affect each other in the course of treatment, while they are frequently treated as separate conditions nowadays. Identifying factors, which influence the course of the trauma-related and personality disorders, allows making predictions about the future course and offers indicators for treatment. Furthermore, the study can contribute to improve diagnosing trauma-related disorders and personality disorders as well as provide knowledge of prognostic variables that may allow the prognosis of an individual patient and the pre-classification/stratification of patients in outcome studies.

## Abbreviations

ANCOVA: Analysis of Covariance
BAI: Becks Anxiety Inventory
BPD: Borderline Personality Disorder
CAPS: Clinician Administered PTSD Scale
CLPS: Collaborative Longitudinal Personality disorders Study
DES: Dissociative Experience Scale
DESNOS: Disorders of Extreme Stress Not Otherwise Specified
DID: Dissociative Identity Disorder
DSM-IV: Diagnostic and Statistical Manual of Mental Disorders
GAF: Global Assessment of Functioning
IDS: Inventory Depression Scale
MSAD: McLean Study of Adult Development
NEO-PI-R: Neuroticism, Extraversion and Openness Personality Inventory - Revised
PBI: Parental Bonding Instrument
PTSD: Post Traumatic Stress Disorder
RCT: Randomized control trial
SCID-D: Structured Clinical Interview for DSM-IV Dissociative Disorders
SCL-90-R: Symptom Check List Revised
SIDES: Structured Interview for Disorders of Extreme Stress
SIDP-IV: Structured Interview for Personality Disorders
SIPP-118: Severity Indices of Personality Problems
STI: Structured Trauma Interview
